### Hypotheses

Our central hypotheses are that frontal pole iTBS will be safe, feasible, and tolerable among veterans with mTBI based on existing literature that suggests frontal pole iTBS is as safe and tolerable as iTBS performed elsewhere [23,25,62]. Similarly, iTBS, when administered to individuals with mTBI is as safe and tolerable as in individuals without mTBI [63]. Given that we are using an established iTBS protocol within the established TMS safety guidelines [84], we do not anticipate significant AEs.

We further hypothesize that social and occupational functioning, negative urgency impulsivity, and SI will be improved for individuals who receive active-iTBS compared with those who receive sham-iTBS. Even if only a single domain improves, we consider this a positive finding.

In addition, we hypothesize that resting-state functional connectivity between the VMPFC and the limbic system (especially the amygdala and anterior cingulate cortex) will be strengthened for the active-iTBS group compared with the sham-iTBS group. We also expect that veterans with increased connectivity between these regions of interest (ROIs) will likely show the most functional improvements.

Pending the results of this pilot trial, larger-scale RCTs may be warranted to establish the efficacy of frontal pole iTBS for social and occupational functional deficits, negative urgency impulsivity, and SI.

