### Analytic Plan

A statistical significance level corresponding to α=.05 will be used to test hypotheses.

Descriptive statistics of feasibility, safety, and tolerability measures will be computed for all participants and compared between active- and sham-iTBS groups. We will calculate the categorical variables’ frequencies and compare them using chi-square analyses for the descriptive statistics [126]. For the continuous variables (ie, daily pain ratings), we will compute mean, median, range, and SDs and compare using 2-tailed *t* tests.

For functional outcome measures, we will estimate a mixed model ANOVA to measure differences within-participants (how the SOFAS changes over time), between-participants (how the SOFAS differs between active and sham iTBS), and whether there is a significant interaction between time and treatment [127]. We will assume equal variance between test and control groups [128]. If the variance is unequal, we may transition to a generalized linear mixed (GLM) effects model [129].

For our neuroimaging analysis, to evaluate the VMPFC to the amygdala and anterior cingulate relationships and how they change before and after treatment, we will define ROIs for the amygdala and anterior cingulate with clear anatomical boundaries identified using Freesurfer [130]. Average time-series data will be extracted, and GLM will be used to quantify the relationship between the seeds and targets. The GLM results will yield individual *r* values (ie, correlations), which will be normalized into *Z* scores using Fisher R-to-Z transformation [131]. The individual maps of *Z* scores will be the primary measure of connectivity between the seed and target ROIs. We will then implement an ROI-to-ROI analysis within the connectivity toolbox to evaluate resting-state functional connectivity between the amygdala, anterior cingulate, and VMPFC [132]. We will assume a normal distribution and use Fisher’s *Z* test to compare active-iTBS and sham-iTBS groups, both before and after treatment [133]. We will adjust for a priori covariates, including age, sex, and baseline psychiatric diagnoses. All analyses will be corrected for multiple comparisons using false-discovery rate correction. We will use linear mixed models to test how connectivity changes correspond to functional and mental health outcome changes, with functional and behavioral measures included as the dependent variables [134].

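### The only between-arm connectivity test is Fisher's Z test run separately before and after treatment: it makes no use of baseline connectivity, does not compare change, and conflicts with the stated covariate adjustment

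*Protocol article*

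**What the plan says.** The Hypotheses section of the protocol article expects that resting-state connectivity between the ventromedial prefrontal cortex and the limbic system "will be strengthened for the active-iTBS group compared with the sham-iTBS group". The neuroimaging paragraph of the Analytic Plan sets the same target, namely these "relationships and how they change before and after treatment".

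Each participant's correlations are put through the Fisher r-to-z transformation, and the resulting Z "scores will be the primary measure of connectivity between the seed and target ROIs". The arms are then to be compared by Fisher's Z "test to compare active-iTBS and sham-iTBS groups, both before and after treatment". Two sentences follow directly: "We will adjust for a priori covariates, including age, sex, and baseline psychiatric diagnoses", and "All analyses will be corrected for multiple comparisons using false-discovery rate correction".

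Change in connectivity appears once more, in linear mixed models that "test how connectivity changes correspond to functional and mental health outcome changes". Those models have the clinical measures as dependent variables. For SOFAS, by contrast, the same section specifies a time-by-treatment interaction.

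**The concern.** There are two separate problems.

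**The contrast.** The hypothesis concerns a difference between arms in how connectivity changes. The plan names two cross-sectional comparisons instead. It gives no arm-by-time term, no comparison of change between arms and no baseline-connectivity covariate. The first of the two comparisons is made between randomised groups before any treatment, so a significant result there can only reflect chance.

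**The test.** The data are one transformed score per participant and pair of regions of interest (ROIs). Fisher's Z test in its usual sense compares two independent correlations, with variance 1/(n1−3) + 1/(n2−3). That variance describes the sampling error of a correlation computed over n independent pairs. It does not describe how much connectivity varies between people, and the test has no place for age, sex or diagnosis. The named test and the next sentence therefore cannot both be carried out as written.

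At stake is the mechanistic aim, one of the study's stated objectives. Its only between-arm test could be invalid or, at best, less precise than the data allow.

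**Working it through.** The plan states no sample size, power or standard error (SE) for the imaging test, so there is no figure to reproduce.

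**Inputs from the protocol**
- 28 per arm and 10% attrition (Power Analysis and Sample Size Justification): 28 × 0.9 = 25.2, so about 25 per arm with a second scan.
- "A statistical significance level corresponding to α=.05 will be used to test hypotheses" (taken as two-sided, which is an assumption for the imaging test).

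**Assumptions, not in the protocol**
- SD of z scores between participants: 0.2 to 0.3.
- Volumes per scan: 240.
- Treatment effect: 0.5 SD.
- Pre-post correlation ρ: 0.3, 0.5 or 0.7.

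**Reading 1: the literal test of two correlations**

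The SE needed for participant-level scores is SD × √(2/25). This is 0.2 × 0.2828 = 0.057 and 0.3 × 0.2828 = 0.085.

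The SE that the test would use depends on what n is:

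| n taken as | SE used | Consequence |
|---|---|---|
| Participants (25 per arm) | √(2/22) = 0.302 | SE too large by 0.302/0.085 = 3.6 to 0.302/0.057 = 5.3 times |
| Volumes in one scan (240) | √(2/237) = 0.092 | False-positive rate about 0.15% to 3.4% |
| Volumes pooled over an arm (25 × 237) | √(2/5925) = 0.018 | False-positive rate about 52% to 67% |

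The false-positive rates are 2 × [1 − Φ(1.96 × SE used / SE needed)].

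In the first row, significance requires a difference of 1.96 × 0.302 = 0.591. A true difference of 0.20 with SD 0.3 falls short of that by (0.591 − 0.20)/0.085 = 4.6 standard errors, so power is practically zero. The test is too conservative in the first two rows and far too liberal in the third. The document does not say which n applies.

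**Reading 2: a z or t test on participants' z scores**

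The SE is then the empirical one and is correct. Simulation under the null (28 per arm, 20,000 trials for each ρ) gave a rejection rate of 4.8% to 5.1% for the post-treatment comparison. It leaves chance imbalance uncorrected, however. Among simulated trials whose baseline arm difference exceeded one standard error, it rejected in 6%, 9% and 12% at ρ = 0.3, 0.5 and 0.7.

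Power for 0.5 SD comes from the noncentral t, with noncentrality (0.5/f) × √(n/2). The factor f is 1 for post-treatment only, √(2(1−ρ)) for a change score and √(1−ρ²) with baseline adjustment:

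| Per arm | ρ | Post only | Change score | Baseline-adjusted |
|---|---|---|---|---|
| 28 | 0.3 | 45% | 34% | 49% |
| 28 | 0.5 | 45% | 45% | 56% |
| 28 | 0.7 | 45% | 66% | 73% |
| 25 | 0.3 | 41% | 31% | 44% |
| 25 | 0.5 | 41% | 41% | 52% |
| 25 | 0.7 | 41% | 61% | 68% |

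Baseline adjustment has the highest power in every row. A raw change score is worse than post-only when ρ is below 0.5, so adjustment is the better way to use the first scan.

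**The case against.** The strongest defence is that the plan gives no variance formula. The surrounding sentences treat the participant's z score as the measure, assume normality and adjust for covariates. That points to a participant-level analysis with a correct SE under a loose name. This stands, and a reader who infers that the imaging results will certainly carry wrong error bars goes beyond the text. The literal reading remains open, because the r-to-z transformation is named separately from the test and each has its own reference. Either way, the name and the covariate adjustment have to be reconciled.

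A reader might also infer that the hypothesis goes untested. It does not: comparing randomised arms after treatment is a valid test of a treatment effect, and the loss is in precision and protection against imbalance. One qualification is that only participants who finish all 10 sessions are asked back for the second scan (Study Procedures), so the comparison is among completers.

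Two further inferences lack support. The baseline scan is not wasted: it enters the pre-treatment comparison and the models relating connectivity change to clinical change. Nor does the plan say that significance after treatment but not before will count as success.

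Finally, this is a condensed article and model detail may sit in a fuller plan. That would excuse silence, but here a specific test and two specific comparisons are stated.

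**Conclusion.** The point holds as an analysis choice that should be fixed. The hypothesis and the paragraph's own aim concern change, yet no between-arm analysis compares change or uses baseline connectivity, and the pre-treatment arm test is uninformative about treatment. This does not depend on any assumption.

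The error in the SE is conditional on the literal reading of Fisher's Z test. Its size rests on the assumed SD, and its direction rests on an n that the document does not give. A headline false-positive rate of 52% to 67% would be unsafe, since it needs volumes pooled over all participants in an arm.

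Under the charitable reading, the cost at 28 per arm is 45% power instead of 49% to 73%, given a 0.5 SD effect and pre-post correlations of 0.3 to 0.7. The matter affects a mechanistic aim of a pilot trial and leaves the primary SOFAS analysis untouched.

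**What to change.** Replace the Fisher's Z test sentence with a participant-level linear model for each pre-specified ROI pair. The post-treatment z score is the outcome, and arm, pre-treatment z score, age, sex and baseline psychiatric diagnosis are the predictors. Take the arm coefficient as the test of the imaging hypothesis and apply the false-discovery-rate correction across the ROI pairs. Drop the pre-treatment between-arm test. Keep the r-to-z transformation, which is appropriate.

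The cost is a change of wording. The model uses z scores that will be extracted anyway, and it needs no further scans or participants.

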To inform future research studies, we will estimate regression models that include additional covariates such as demographics, psychotropic medication use, comorbid psychiatric diagnoses, and scores on the Inventory of Depressive Symptomatology, Self-Report and the PTSD Checklist for DSM-5, in addition to testing our hypotheses for the primary and secondary outcomes.

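### The models relating connectivity change to outcome change are described without a treatment term, so an arm effect on both measures could appear as a link between them

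*Protocol article*

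**What the plan says.** In the neuroimaging paragraph of the Analytic Plan, the last analysis is: "We will use linear mixed models to test how connectivity changes correspond to functional and mental health outcome changes". The outcomes sit on the left-hand side of these models, which are to be fitted "with functional and behavioral measures included as the dependent variables". This fixes the model class, the explanatory quantity and the dependent variables. It mentions neither treatment arm nor a subset of participants.

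Two covariate statements stand nearby. The same paragraph says "We will adjust for a priori covariates, including age, sex, and baseline psychiatric diagnoses". The closing paragraph of the Analytic Plan says "we will estimate regression models that include additional covariates such as demographics, psychotropic medication use, comorbid psychiatric diagnoses", then adds depression and PTSD scores. Neither list names arm, and neither claims to be complete.

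Treatment is named in the other comparative analyses. The SOFAS model tests "whether there is a significant interaction between time and treatment", and the connectivity comparison will "use Fisher’s *Z* test to compare active-iTBS and sham-iTBS groups, both before and after treatment".

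The Hypotheses section expects functioning to improve, and VMPFC-limbic connectivity to strengthen, under active relative to sham stimulation. It then adds: "We also expect that veterans with increased connectivity between these regions of interest (ROIs) will likely show the most functional improvements". That sentence is not limited to one arm.

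**The concern.** If active stimulation moves both connectivity and functioning, randomised arm is a common cause of the two change scores. Active participants then tend to be high on both and sham participants low on both. A model without arm picks up that separation as a positive slope, even if connectivity change says nothing about improvement among participants treated alike. The third hypothesis could then appear confirmed simply because the first two hold.

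This matters because of how the result is to be used. Under Principal Findings in the Discussion, the connectivity changes are expected to inform how neuromodulation works, and changes that track symptoms may point to future stimulation sites. Both uses need an association beyond the arm difference that the trial already tests separately.

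**Working it through.** **Inputs from the protocol** (Power Analysis and Sample Size Justification): 50 evaluable veterans, taken as 25 per arm; SOFAS change of 13 points in the active arm and 0 in the sham arm; SD 15; α = 0.05, taken as two-sided; 56 enrolled, 28 per arm.

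**Assumed:** the shift in connectivity change between arms, for which the protocol gives no figure. The range shown is 0 to 1.5 SD.

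**Step 1: the plan's own figure.** The stated power is 82%. If SD 15 is the SD of change, a two-sample t test with 25 per arm has 85.1% power. If SD 15 is the SD at each visit, the SD of change is 15·√(2(1−ρ)). At ρ = 0.45 this is 15·√1.1 = 15.7, and power is 81.7%. The protocol gives no ρ, so its reading of SD 15 is not settled. The standardised outcome shift is 13/15 = 0.87 on the first reading and 13/15.7 = 0.83 on the second. The difference is small, and 0.87 is used below. The stated power is not in dispute here. The inflation for attrition reproduces: 50/0.9 = 55.6, rounded up to 56.

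**Step 2: correlation induced by arm alone.** Let the two change scores be independent within each arm, with 1:1 allocation and standardised arm shifts d₁ (connectivity) and d₂ (outcome). The between-arm covariance is d₁d₂/4 and the total variances are 1 + d₁²/4 and 1 + d₂²/4, so

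r = (d₁d₂/4) / √[(1 + d₁²/4)(1 + d₂²/4)].

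For d₁ = d₂ = 0.867, d²/4 = 0.188 and r = 0.188/1.188 = 0.158.

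**Step 3: rejection rate.** 40,000 simulated trials per scenario, simple change scores, two-sided 5% test of the association, no multiplicity correction, d₂ = 0.87, no association within either arm:

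| Connectivity shift (SD) | Induced r | No arm term, 25 per arm | No arm term, 28 per arm | With arm term, 25 per arm |
|---|---|---|---|---|
| 0 | 0.00 | 4.9% | 4.9% | 4.8% |
| 0.3 | 0.06 | 6.9% | 7.2% | 4.9% |
| 0.5 | 0.10 | 10.3% | 10.9% | 5.0% |
| 0.8 | 0.15 | 17.9% | 19.5% | 4.9% |
| 0.87 | 0.16 | 19.9% | 21.5% | 5.0% |
| 1.0 | 0.18 | 24.1% | 26.6% | 5.1% |
| 1.5 | 0.24 | 39.8% | 44.0% | 5.1% |

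Setting the outcome shift to zero instead, with a connectivity shift of 0.8 SD, gives 4.8%. Both effects are needed for inflation.

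**Hand check at 0.87/0.87:** atanh(0.158)·√(50−3) = 0.159 × 6.86 = 1.09. The chance of exceeding 1.96 is then 1 − Φ(0.87) ≈ 0.19, in line with the simulation.

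**The case against.** The strongest reply is that the article is silent on arm and does not exclude it. One sentence gives a model class, a predictor and dependent variables, with no full list of fixed effects. Both covariate lists are open. The first follows directly on the active-versus-sham comparison, where arm is the contrast and would not be listed as a covariate. The full protocol or SAP may well include arm. A reader might infer that the plan prescribes a pooled analysis unadjusted for arm. The text does not say that, and pooling is an inference. The Discussion also speaks of changes among those who respond to iTBS, which could mean an analysis within the active arm, where this problem would not arise.

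That reply limits the strength of the point but does not remove it. The article does describe this model, it names treatment for the neighbouring analyses, and it states the association hypothesis for veterans in general.

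It is also fair to say that the Hypotheses section does not specify a within-arm relationship. An overall association is a legitimate description. It cannot, however, support a mechanistic reading beyond what the two arm comparisons already show.

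The size is open to challenge too. The connectivity shift is assumed, and inflation is small at 0.3 SD. The simulation uses simple change scores, not the planned mixed model, and ignores the planned false-discovery-rate correction. That correction does not remove the bias, but 20% should not be read as the trial's actual error rate.

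A reader might further infer that the model would mislead about who will respond to treatment. The documents do not support this. The Discussion's Conclusions tie prediction to pretreatment imaging. The Strengths section mentions imaging before and after treatment in the same sentence as likely responders, but does not link prediction to the change-on-change model.

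**Conclusion.** The point holds in a conditional form. As described, the connectivity-outcome models carry no treatment term. If the arms are analysed together and active iTBS raises both measures, an association can arise with none inside either arm. With the protocol's SOFAS shift taken as 0.87 SD and 25 per arm, an uncorrected 5% test rejects in roughly 7% to 24% of trials for assumed connectivity shifts of 0.3 to 1.0 SD. It stays near 5% if either effect is absent or if arm is in the model. The induced correlation is modest, 0.16 when both shifts are 0.87 SD.

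This concerns secondary mechanistic models in a pilot trial. The primary SOFAS time-by-treatment test names treatment and is unaffected, and no claim is made about the prediction of response. The change is still worth making, because it decides whether these models can add anything to the two arm comparisons.

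**What to change.** State that the connectivity-outcome models include treatment arm as a fixed effect. Base any mechanistic reading on the arm-adjusted connectivity coefficient, and report the arm-by-connectivity interaction as exploratory. If an analysis within the active arm alone was meant, say so. If the full protocol or SAP already includes arm, a sentence confirming it is enough.

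The cost is one degree of freedom for the arm term, plus one more in the exploratory model that carries the interaction. No new data are needed. The Results section reports 2 participants enrolled as of July 2024 and dissemination by March 2028.

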## Results

This study was funded in April 2023 and began enrolling participants in July 2024. As of July 2024, there are 2 participants enrolled in the study. Data will be analyzed and study results will be disseminated on or before the project’s end date in March 2028.

## Discussion

### Principal Findings

This novel protocol represents the first pilot RCT for frontal pole iTBS for mTBI, negative urgency impulsivity, and suicidality. We hypothesize that iTBS administered to the frontal pole in US veterans with mTBI, impulsivity, and suicidality will be safe and well tolerated as studies show that both TMS and iTBS appear safe and effective when administered to other anatomical sites in individuals with mTBI [23-26]. Furthermore, studies demonstrated frontal pole iTBS is tolerable with good safety outcomes in individuals without mTBI [63].

We hypothesize that we can improve social and occupational functioning, impulsivity, and SI among US veterans with mTBI. Other studies have specifically found meaningful change in both the UPPS-P and SOFAS over a 2-week neuromodulation intervention period among individuals with major depression [90,135]. Several repetitive TMS (the precursor to iTBS) trials among individuals with SI and major depression have shown reductions in suicidality [71-74]. We anticipate these results will generalize to individuals with mTBI when treated with iTBS [72,136].

Finally, we hypothesize that we will be able to identify changes in neural connectivity among individuals who respond to our iTBS protocol by comparing pretreatment fMRIs with posttreatment fMRIs. Several studies on both iTBS and TMS, administered to the DLPFC, of a variety of treatment durations, showed increased connectivity between the frontal cortex and areas of the limbic system [137]. We expect to see similar results with iTBS administered to the VMPFC.

We will add to the existing literature in several ways. First, there are no widely established treatments for poorer functional outcomes, suicidality, or impulsivity that occur in the context of mTBI. If we can develop an effective intervention that targets all of these likely interrelated conditions, we will be adding important findings to the literature base and we could also improve the quality of life and treat SI among people with mTBI. By further establishing the frontal pole as a tolerable and effective iTBS stimulation site, we could also encourage other researchers to explore this site for potential therapeutic benefit for a variety of conditions. Finally, by identifying fMRI connectivity changes before and after iTBS treatment, we will add to the literature base regarding how neuromodulation works mechanistically, which is still unclear. Moreover, if we can identify specific fMRI connectivity changes correlating to symptomatic changes, it may help us identify future neuromodulatory treatment sites of interest, to continue to further explore this very promising treatment modality.

